### Intervention program

The following steps were used to create the first video-delivered school-based gatekeeper program in China. First, the Delphi method was utilized, engaging a group of experts who independently rated their agreement with the proposed content for the program in a multi-stage, iterative manner. Experts were individually invited through email if they were specialists with relevant suicide prevention or intervention experience. After recruitment, two rounds of structured Delphi surveys were used to collect expert feedback on the following aspects: the importance of the training content, the feasibility of the training method, the achievement of the training objectives, and the appropriateness of the training materials. In the first round, 157 items were reviewed by 34 panel members, and in the second round, 55 items were reviewed by 31 panel members. Items that were endorsed by 80% or more of the panel members were adopted immediately. Overall, 201 statements were endorsed to be included in the Life Gatekeeper Training Program [28]. Then, two single-arm sequential pilot studies with 57 teachers fromtwo schools were conducted and evaluated for the program’s effectiveness, employing in-person training and then hybrid delivery strategies (i.e., remote and in-person training)  followed by the TTT approach. Both delivery methods have been proven effective, with the TTT version, in particular, showing advantages in practical implementation [30]. Finally, we modified the program and generated the final version of the Life Gatekeeper Training Program based on the findings of the pilot studies. The first school-based gatekeeper program for primary and secondary school teachers has been established in its final form.

The Life Gatekeeper Training Program consists of two main packages. The first package comprises eight sessions of video-recorded training (Table 1), including psychoeducational content, animated films, role-playing, and group discussions, with the training concluding with online group supervision by crisis intervention specialists. For instance, when it is time for the group discussion, there will be a prompt in the video indicating, “It’s time for the group discussion.” A timer will be displayed on the screen, and the instructors or core teachers only need to organize the discussion activity. In addition, the following topics are covered within the program (1) the severity of suicide among children and adolescents, and the common feelings of suicidal persons, (2) establishing a correct understanding of suicide, (3a) risk factors associated with suicide, (3b) identifying the warning signs of suicide, (4) the correct way to communicate suicide risk, (5) assessing suicide risk, (6) making a safety plan, (7) teachers communicating with parents about their kids’ suicide risk, psychoeducating parents on how to express support to their kids, and determining subsequent procedures with parents, and (8) any potential barrier that might stop teachers from providing help, and how to overcome it into actual gatekeeping behaviors.

**Table 1 Tab1:** Contents of the Life Gatekeeper Training Program

Section	Theme	Methods of delivery	Length of training
1	The severity of suicide among children and adolescents, and the common feelings of suicidal persons	Video viewing; group discussion	21 min + 07 sec
2	Establishing a correct understanding of suicide	Video viewing; group discussion	22 min + 35 sec
3	Risk factors associated with suicide, identifying the warning signs of suicide	Video viewing; group discussion	22 min + 12 sec
4	The correct way to communicate suicide risk	Video viewing; group discussion; role play	66 min + 48 sec
5	Assessing suicide risk	Video viewing; role play	47 min + 27 sec
6	Making a safety plan	Video viewing; role play	78 min + 58 sec
7	Teachers communicating with parents about their kids’ suicide risk, psychoeducating parents on how to express support to their kids, and determining subsequent procedures with parents	Video viewing; role play	43 min + 13 sec
8	Any potential barrier that might stop teachers from providing help, and how to overcome it into actual gatekeeping behaviors	Video viewing; group discussion	15 min + 40 sec

*min* minutes, *sec* seconds

All participants will also receive another package, including a training manual, an appendix, a pamphlet for parents, a pamphlet for children and adolescents, and an information sheet summarizing mental health service resources and crisis hotline numbers, in addition to these recordings. The training manual and appendix will include everything that will be covered in training. The pamphlet for parents can be used to educate parents of at-risk students about child and adolescent suicide and how to seek help. During a crisis, students can use the pamphlet for children and adolescents to find support for themselves. Meanwhile, teachers can provide at-risk students and their parents with an information sheet on mental health services and crisis hotline numbers, so that they can refer students to receive professional assistance as needed. These materials will be printed out in advance and utilized for role-plays, group discussions, and note-taking during the training. All required materials were stored in a password-protected cloud storage platform to make the materials easily accessible.

The intervention is delivered in a single day, with a break in the middle. Only members in the intervention group will have access to all resources, including video clips, as they are only available to individuals who consent to participate. Nevertheless, teachers are free to hand out the pamphlet for parents, the pamphlet for children and adolescents, and the summary sheet later in their work with at-risk students. The fidelity checklist was employed to ensure that the trainers followed each step correctly, and to guarantee consistent audiovisual delivery and adherence to the procedure.

### Outcomes

The outcome measures are summarized in Table 2. All participants will be assessed for the primary and secondary outcomes, while only participants in the intervention group will be assessed for the process evaluation outcomes at the *t*
_2_ questionnaire.

**Table 2 Tab2:** O﻿utcome measures for the randomized controlled trial of the Life Gatekeeper Training Program

Measurements	Aim	t_1_	t_2_	t_3_	t_4_
**Primary outcomes**					
Short form of the stigma of suicide scale – stigma subscale	Stigmatized attitudes against suicide	✓	✓	✓	✓
Short form of the literacy of suicide scale	Suicide literacy	✓	✓	✓	✓
The willingness to intervene against suicide questionnaire – perceived behavioral control subscale	Perceived competence to intervene	✓	✓	✓	✓
The willingness to intervene against suicide questionnaire – willingness to intervene subscale	Willingness to in intervene	✓	✓	✓	✓
**Secondary outcomes**					
Gatekeeper behaviors	Behaviors as gatekeeper after intervention			✓^*^	✓
**Process evaluation**					
Perceived intervention quality	General satisfaction, skills acquired, knowledge gained, willingness to recommend the intervention		✓		
Fidelity Checklist	Objective quality of delivering of the intervention		✓		

*Note*. The ^*^ represents a measure used exclusively for the intervention group

### Primary outcomes

#### Stigma of suicide scale

The Chinese version of the short form of the Stigma of Suicide Scale (SOSS) will be used to measure participants’ stigmatized attitudes against suicidal individuals [32]. The SOSS has three subscales; the current study will utilize the stigma subscale to measure participants’ aversive attitudes toward suicidal individuals [32]. The original stigma subscale of the SOSS has eight items, while the Chinese version included five items after local adaptation based on psychometric tests conducted with Chinese participants [33]. Participants will indicate their attitudes toward each item by using a 5-point Likert scale from 1 (strongly disagree) to 5 (strongly agree). The Chinese short form SOSS has been shown to have good psychometric properties as a measurement capturing the stigma of suicide in the Chinese population [33]. The total score is the sum of all items, with higher scores indicating more severe stigmatized attitudes.

#### Literacy of suicide scale

The Chinese version of the short form Literacy of Suicide Scale (LOSS) will be used to measure participants’ suicide literacy [33]. The LOSS is a 11-item scale covering a series of statements about suicidal behaviors and suicidal individuals. The LOSS measures one’s suicide literacy regarding the nature, symptoms, and help-seeking methods of suicide by having participants indicate whether they think a statement is true [34]. Participants will indicate their attitudes for each item by choosing from True, False, or Not sure, while a correct answer will be awarded 1 point. The Chinese short form LOSS has been shown to have good psychometric properties as a measurement capturing suicide literacy in the Chinese population [33]. The total score is the sum of correct items, with higher scores indicating greater literacy of suicide.

#### Perceived competence, and willingness to intervene against suicide questionnaire

The Chinese version of the Willingness to Intervene Against Suicide Questionnaire (WIS), will be used to measure participants’ perceived competence and willingness to intervene with students with suicidal risk [35]. The WIS, developed through three studies involving American college students, consists of four subscales. The current study will use the perceived behavioral control subscale to measure participants’ perceived competence to intervene and use the willingness to intervene subscale to measure participants’ willingness to intervene with students with suicidal risks. The perceived behavioral control subscale and the willingness to intervene subscale have 20 and 22 items respectively, capturing a range of methods of intervening with students with suicidal risks. Participants will use a 5-point Likert scale to indicate whether they feel confident or are willing to intervene with a suicidal student through different methods in the perceived behavioral control subscale and the willingness to intervene subscale, respectively. The WIS showed good psychometric properties as a measurement capturing one’s perceived competence and willingness to intervene with a student with suicidal risk [36]. The Chinese version was translated and reviewed by two researchers with previous experience in suicide research who are fluent in both Chinese and English. The total score is the sum of each item for both subscales, with higher scores indicating greater perceived competence and willingness to intervene.

### Secondary outcome

#### Gatekeeper behaviors

The study will also measure the gatekeeper behaviors of participants in both the intervention and control groups at 12 months post-intervention. To measure short-term behavioral changes, the intervention group will also report behaviors at the 6-month mark [37, 38]. This measurement will be conducted using four individual questions that have been adjusted from previous studies to enable a rigorous comparison, taking into account the lagging nature of the observation period for behavior changes. Following questions will be asked (1) During the 6 months/12 months after the training, have you identified any students who may be at risk of suicide (or are experiencing psychological distress)? (2) Among these students, how many have you discussed potential suicide risks (or their psychological distress) with? (3) Among these students, how many have you discussed their suicide risk (or their psychological distress) with their parents? (4) Among these students, how many have you referred to mental health professionals or specialist clinics? Percentage scores will be calculated for each intervention method by comparing the number of students they intervened with to the number of students they identified. These scores will range between 0 and 100%, with a higher percentage indicating a higher frequency of gatekeeper behaviors.

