## Methods

### Trial design

The participant flow and research design are depicted in Fig. 1. This trial will be a two-arm, non-blinded randomized controlled trial (RCT) with two parallel groups: a wait-list control group and a Life Gatekeeper intervention group. All qualified teachers in the same school will be assigned to either the intervention group or the control group through cluster sampling. The day before intervention group training, participants will be required to take a baseline survey (*t*
_1_). The same day the training is finished, the post-test survey (*t*
_2_: immediately following the intervention) will be carried out. Six months (*t*
_3_) and twelve months (*t*
_4_) after the *t*
_2_ survey, respectively, follow-up questionnaires will be completed. The survey forms will be used for all polls, and the same time frame applies to the control group. The Standard Protocol Items: Recommendations for Interventional Trials (SPIRIT) standards were followed in the preparation of this manuscript (Supplementary Material 1).

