### Procedure

Each school will be randomly assigned to either the intervention group or the control group using cluster sampling. The researchers will inform participants of their group allocation. Participants can learn about the Life Gatekeeper training study by scanning a given QR code and then reading a detailed explanation of its purposes and procedures. All participants will be asked to provide informed consent, and the data gathered will be kept confidential. Teachers will be trained using a method referred to as the TTT model. In the Life Gatekeeper Training Program, professional instructors first conduct primary remote training for the intervention group’s core teachers. Over the week following the primary training, the intervention group’s core teachers conduct secondary in-person training for all head teachers and teaching staff from their own schools. To ensure the intervention is delivered as specified in the intervention protocol or manual, professional instructors and core teachers will complete the fidelity checklist while carrying out each training [31]. Each participant will complete the baseline survey (*t*
_1_) one day before the training of the intervention group, and the post-test survey (*t*
_2_) immediately after the training. These participants will also receive follow-up surveys at 6 months (*t*
_3_) and 12 months (*t*
_4_) after *t*
_2_. Surveys at time points 1, 2, 3, and 4 will be carried out synchronously for both the control and intervention groups. Participants in the control group, including core teachers, head of class teachers, and teaching staff, will be offered the Life Gatekeeper Training Program after the 12-month follow-up. Training certificates issued by the research team will be used to promote participant retention. Data collection training will be conducted for the team members before the study, and core teachers will also be trained to cooperate with the team members in collecting data in their respective schools. If any participant discontinues participation between baseline and the 12-month follow-up, no additional data will be collected.

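### The 12-month gatekeeper-behaviour question counts from a training that control teachers have not had, so its recall window is undefined in one arm; the 6-month behaviour data have no comparator

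*Protocol article*

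**What the plan says.** The trial compares "a wait-list control group and a Life Gatekeeper intervention group". Under Procedure, control participants "will be offered the Life Gatekeeper Training Program after the 12-month follow-up", and participants are told their group.

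The Gatekeeper behaviors section plans to "measure the gatekeeper behaviors of participants in both the intervention and control groups at 12 months post-intervention". It adds that "the intervention group will also report behaviors at the 6-month mark", in order to look at short-term change. Four questions are listed. The first reads "During the 6 months/12 months after the training, have you identified any students who may be at risk of suicide", and the other three refer back to the students identified there. No separate wording for controls is given. Each teacher's scores are percentages from 0 to 100%: students with whom a given step was taken, divided by students identified. The section says the items were adapted so that the comparison would be rigorous.

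Table 2 describes the aim of the measure as "Behaviors as gatekeeper after intervention". It ticks t3 with a star and t4 without one, and leaves t1 and t2 blank. Its note says the star "represents a measure used exclusively for the intervention group". The text introducing the table says "All participants will be assessed for the primary and secondary outcomes".

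**The concern.** The item asks a teacher to look back over a period that starts at the training. At 12 months a wait-list teacher has had no training and, being unblinded, knows it. Such a teacher may answer 'none', substitute some other period or other training, or skip the item. An intervention teacher has a clear starting date. The two arms could then give different answers even if they behaved identically.

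This matters because behaviour is the trial's only secondary outcome, the Discussion's hypothesis ends in increased gatekeeper conduct, and 12 months is the only time at which both arms report it. The 6-month data cannot fill the gap, since controls do not answer the behaviour items then.

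**Working it through.** The plan gives no figure on this point to reproduce. The check sets the sections side by side and then follows a 'none' answer through the scoring.

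**Step 1: the recall window in each arm** (Gatekeeper behaviors, Procedure, Table 2 and its note)

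| | Intervention | Control |
|---|---|---|
| Trained by the 12-month survey | yes | no, offered afterwards |
| Start of the printed window at t4 | date of training | none |
| Behaviour items at t1, t2 | no | no |
| Behaviour items at t3 | yes | no |
| Behaviour items at t4 | yes | yes |
| Behaviour assessments in total | 2 | 1 |

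**Step 2: effect on the first item.** Let p be the share of control teachers who identified at least one student, and s the fraction of those who answer 'none' only because they were not trained. The observed control share is p(1 − s), which is below p whenever s > 0. On this item the error makes the control arm look less active.

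**Step 3: effect on the percentage scores.** A 'none' answer makes the denominator zero, so the teacher has no score. Among control teachers who did identify a student, let m1 be the mean score of those who say so and m0 the mean of those lost.

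- True control mean: (1 − s)m1 + s·m0
- Observed control mean: m1
- Error: m1 − [(1 − s)m1 + s·m0] = s(m1 − m0)

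If the loss is unrelated to behaviour, m1 = m0 and the error is zero. If less active teachers are lost, m1 > m0 and the control mean is too high, which works against the programme. If more active teachers are lost, the reverse holds. Scores run from 0 to 100, so the error cannot exceed 100s points in either direction: 10, 20 or 30 points for assumed s of 0.1, 0.2 or 0.3. These are outer limits and not expected values; the document gives no s, m1 or m0.

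**Step 4: the 6-month data.** With no control observations at t3, there is no between-arm contrast. With no behaviour items at t1, there is no before-after contrast either. The t3 and t4 windows both start at the training, so the first 6 months lie inside the 12-month window, and t3 cannot serve as a baseline for t4.

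**Step 5: was the t3 restriction forced?** No. The Procedure section runs all four surveys at the same time in both arms, so controls complete a 6-month survey in any case.

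**The case against.** The best defence is that the intended control window is clear. Trial design says the same time frame applies to controls, and the Procedure section times every survey from the intervention group's training and runs the surveys together. The questions are also an English template that covers 6 and 12 months, and the form that controls received is not shown. This shows that the intended window is probably the same 12 calendar months. It does not rescue the item: those sentences govern when surveys are sent, not what a control teacher reads, and the one wording printed gives that teacher no starting date. If a control version exists, the article should print it.

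Four stronger readings are tempting but not supported.

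- A reader might infer a bias of 1/(1 − s) in favour of the programme, that is 1.11, 1.25 or 1.43 for assumed s of 0.1, 0.2 or 0.3. That is the ratio of shares identifying any student when the true shares are equal. The defined outcome is a percentage among students identified. There, loss unrelated to behaviour leaves an expected ratio of 1.00, and related loss can go either way.
- A reader might infer that the Outcomes section contradicts Table 2. Its sentence contrasts primary and secondary outcomes with process outcomes and does not claim every time point. Controls are assessed on the secondary outcome, at t4.
- A reader might infer that only the intervention arm is prompted about intervening at 6 months. Both arms complete the perceived behavioural control and willingness subscales then (20 and 22 items). What differs is the four behaviour questions, and their added effect on 12-month reports is possible but unquantified.
- A reader might infer that the protocol claims a 6-month behaviour effect. It does not. The restriction is disclosed, and the between-group model in Statistical analysis is specified for primary outcomes.

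**Conclusion.** The concern holds in limited form. As printed, the behaviour item has no defined recall window for control teachers at 12 months, in the only between-arm comparison of the only secondary outcome. The consequence is a possible understatement of the control share identifying any student, plus differential selection into the percentage scores. Neither can be sized from the document, and for the percentage scores the direction is also unknown. The 6-month behaviour data describe one arm, without baseline or control, and cannot show a programme effect.

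This assumes that controls receive the item as printed. Severity is moderate: no primary outcome is affected, and both arms are surveyed at the same calendar time. Analysis cannot recover a window the respondent was never given, so the wording deserves correction while that is still possible.

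**What to change.** - **t4 form:** use one calendar-anchored wording in both arms, for example 'in the past 12 months' or 'since the survey of [date]', with no reference to training. Carry the same period through the three follow-on questions.
- **If t4 is already collected:** report the exact wording each arm received and state the limitation. Trial status has data collection for the second follow-up complete by September 2023 (recruitment ended by March 2023, plus six months, so this reads as t3) and the final follow-up ending by March 2024. Adding the items for controls at t3 is therefore no longer possible, and the t4 form may or may not still be open.
- **t3 behaviour data:** label them uncontrolled and descriptive, and note the extra 6-month behaviour questions in one arm as a possible limitation of the t4 comparison.
- **Outcomes section:** add the t3 exception to the sentence on who is assessed, for clarity.

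The cost is rewording four online items and a short text edit. The downside is that the t4 wording will differ slightly from the t3 form in the intervention arm. That matters little, because the t3 data are not used for a between-arm comparison.

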## Discussion

### Strengths of the study

According to our hypothesis, the Life Gatekeeper Training Program for teachers will lessen the suicide stigma while enhancing their knowledge, skills, and willingness to intervene as gatekeepers, leading to increased actual gatekeeper conducts.

To the best of our knowledge, this is the first RCT study to examine a localized gatekeeper program’s effectiveness, including video-delivered components for primary and secondary school teachers. The program is practical due to its strong emphasis on skill acquisition and practice. It is also instantly accessible to participants as all video clips and workbooks can be retrieved through an online platform anytime and anywhere. Along with advancing the field of suicide prevention and intervention study in China, the proposed program will produce valuable and meaningful evidence-based practice and policy benefits for pertinent stakeholders. Ultimately, it could potentially establish a multi-level suicide prevention system that consists of schools, families, and professional psychological institutions, thereby better safeguarding children and adolescents from suicide.

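### The gatekeeper-behaviour percentage divides by the number of students identified, which the training aims to raise, so it does not test whether gatekeeper behaviour increased

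*Protocol article*

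**What the plan says.** The section on gatekeeper behaviors lists four questions.

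- Question 1 asks the teacher: "have you identified any students who may be at risk of suicide (or are experiencing psychological distress".
- Questions 2 to 4 ask how many of those students the teacher talked to, raised with their parents, or referred. The last reads: "Among these students, how many have you referred to mental health professionals or specialist clinics".

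The scoring rule is explicit. Each method of intervening gets its own percentage, formed "by comparing the number of students they intervened with to the number of students they identified". So is its reading: "These scores will range between 0 and 100%, with a higher percentage indicating a higher frequency of gatekeeper behaviors".

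Both arms answer at 12 months, and only the intervention arm answers at 6 months. In Table 2 this is the sole secondary outcome and the sole measure of behaviour; the four primary outcomes are stigma, literacy, perceived competence and willingness. The hypothesis under Strengths of the study is that training improves attitudes and skills, "leading to increased actual gatekeeper conducts".

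Two other places show that identification is a training target. The Introduction names it first among the skills that gatekeeper training gives, and section 3 of the curriculum in Table 1 covers risk factors and recognition of warning signs.

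**The concern.** The hypothesis is about how much gatekeeping takes place. The score measures something else: the share of identified students on whom the teacher then acted. Its denominator arises after randomisation, and the training is meant to increase it. The score therefore gives no credit for finding more students at risk, which is the first step of the behaviour. It can also fall when the additional students are acted on less often, for example because their distress is milder. The sentence that equates a higher percentage with a higher frequency is wrong as written: a teacher who identifies 2 students and talks to 2 scores 100%, while one who identifies 5 and talks to 4 scores 80% with twice as many students helped.

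At stake is the trial's only evidence on what teachers do, as opposed to what they know, feel or intend. A programme that works could be reported as having no effect, or an adverse one, on behaviour.

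**Working it through.** The protocol gives no figure for this outcome, so there is nothing to reproduce. The only documented input is the final sample per arm, 42 schools × 30 teachers = 1,260 (Sample size calculation). All identification and helping rates below are assumptions.

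**1. Direction of the score.** Let control teachers identify m students each on average and help a proportion p of them. Let training add d further students, helped at rate q, and leave the handling of the others unchanged.

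- Helped per teacher: control m·p; trained m·p + d·q. This rises whenever q > 0.
- Score: control p; trained (m·p + d·q)/(m + d). This equals p if q = p and is below p if q < p.

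So for any q above 0 and below p, the score falls while more students are helped. With Poisson counts, the mean percentage among teachers who identified at least one student equals this ratio.

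**2. Numbers, with assumed m = 0.3 and p = 80%.**

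| Scenario | Helped per 100 teachers | Score |
|---|---|---|
| Control | 100 × 0.3 × 0.8 = 24 | 80% |
| Trained, d = 0.3, q = 80% | 100 × 0.6 × 0.8 = 48 | 0.48/0.6 = 80% |
| Trained, d = 0.3, q = 40% | 100 × (0.24 + 0.12) = 36 | 0.36/0.6 = 60% |
| Trained, d = 0.6, q = 50%, and the original 0.3 now helped at 90% | 100 × (0.27 + 0.30) = 57 | 0.57/0.9 = 63.3% |

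In the last row the training also improves the response to students who would have been found anyway, and the score still falls.

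A second set of assumed rates, for referral, gives the same pattern. Per 1,000 teachers, control refers 1,000 × 0.5 × 0.60 = 300 students; trained refers 1,000 × 1.0 × 0.50 = 500. Referrals rise by 200/300 = 67%, while the score falls from 60% to 50%.

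**3. Teachers without a score.** A teacher who identifies nobody has 0/0. With Poisson counts of mean λ the share is exp(−λ):

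| λ | Share with 0/0 | Of 1,260: no score | Of 1,260: score |
|---|---|---|---|
| 0.1 | 90% | 1,140 | 120 |
| 0.25 | 78% | 981 | 279 |
| 0.5 | 61% | 764 | 496 |
| 1 | 37% | 464 | 796 |
| 2 | 14% | 171 | 1,089 |

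If training moves λ from 0.5 to 1, a score exists for 496 control and 796 trained teachers. In the third row of the first table (λ of 0.3 against 0.6) it exists for 1,260 × (1 − exp(−0.3)) ≈ 327 against 1,260 × (1 − exp(−0.6)) ≈ 568. The group with a score would then differ between arms because of the training.

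**The case against.** The percentage has a sound meaning: given that a teacher sees a student at risk, does the teacher act? It allows for unequal exposure to such students, which a count does not. Sections 4 to 7 of the curriculum teach communication, risk assessment, safety planning and contact with parents, so this conditional rate may well rise. The falls shown above come from assumed rates; they show that a reversal is possible, not that it is likely. All of this stands. A reader might infer that the sign of the score cannot be interpreted at all. The document does not support that: as a conditional response rate the sign is readable. It does not answer the stated hypothesis.

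Two other stronger readings also go too far.

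- *Teachers who identify nobody are dropped.* No rule is stated, and the Statistical analysis section specifies a model for the primary outcomes only. A rule may stand in an analysis plan that is not shown. Exclusion is one possibility. Scoring these teachers as 0% would keep them but change what the score means. No such rule repairs the ratio itself.
- *The denominator is never collected.* Question 1 as printed can be answered yes or no, but the scoring rule presupposes a number and the article may paraphrase the form. The wording is unclear; it does not prove that the number is missing.

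Finally, this is a secondary outcome, and the answers to questions 2 to 4 are counts, so a better analysis needs no change of design.

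**Conclusion.** The point holds. The score and its reading are fixed in the protocol article itself, and the sentence linking percentage to frequency is incorrect. The score is blind to a gain in identification when the helping rate is unchanged, and it falls when the extra students are helped at a lower rate and the response to the others does not improve enough to offset this. It therefore does not test the hypothesis of more gatekeeper behaviour. This conclusion about direction needs no particular rate.

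The sizes do rest on assumptions: 24 to 36 students helped per 100 teachers against a score of 80% to 60%, and 90% to 14% of teachers without a score across Poisson means of 0.1 to 2. The loss of randomised comparison is conditional on excluding teachers with 0/0. The grade is should-fix: the outcome is the only behavioural one, but the four primary outcomes do not depend on it.

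**What to change.** - **Between-arm analysis at 12 months.** Use the per-teacher counts from questions 2 to 4 (talked with the student, talked with parents, referred), plus identification from question 1, as a count if a number is recorded and otherwise as yes/no. Include all randomised teachers who respond and keep zeros. Fit a log-link count GEE clustered by school, with a logit link for a yes/no item. GEE is already the planned method for the primary outcomes.
- **Percentages.** Report them as a descriptive conditional response rate among teachers who identified at least one student.
- **Wording.** Delete or correct the statement that a higher percentage means a higher frequency.
- **Question 1.** If the form really asks only yes or no, ask for the number in surveys not yet sent. This is not the main remedy: Trial status reports the second follow-up complete as of September 2023 and expects the last to end by March 2024.

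The cost is a change of analysis text, with no added visits or staff; the counts from questions 2 to 4 are already part of the survey. There are two downsides. Counts do not adjust for differing exposure to students at risk, although randomisation of schools balances this on average. A late change to question 1 could make the intervention arm's 6- and 12-month answers less comparable.
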